### Study aims and approaches

The specific aims for the *Neighborhood & Health Study* are to: (1) assess short-term changes in dietary intake, physical activity, cardiometabolic health indicators, and social connectedness among Texas residents living in the agrihood compared to non-agriculturally-integrated, master-planned neighborhood; (2) document time use with features of the agrihood and assess preferences for built and nature design features to provide resident-driven data for future developments; and (3) examine the resident- and community-level economic benefits of the agrihood.

The study design and selection of measures are guided by the socioecological model, which recognizes that health behaviors are influenced by interacting individual (e.g., diet, physical activity, stress), interpersonal (e.g., social connection), organizational (e.g., community programs), and environmental (e.g., built and natural design features) factors (27). This framework provides a foundation for examining how agrihood design features may affect resident health and wellbeing.

To conduct Aim 1, we will recruit two longitudinal cohorts, one of new agrihood residents (*N* = 175), and one of current comparison neighborhood residents (*N* = 175). Agrihood participants completing the baseline assessment will receive $100, those wearing an accelerometer and completing a mid-point survey will receive $150, and those completing the 6-month follow-up will receive $100. Comparison participants will only complete surveys and will receive $50 for the completion of a survey at each timepoint. Physical assessments will be conducted among agrihood participants by trained clinical staff in Mobile Health Assessment Centers (MHACs), which are mobile clinic spaces specifically designed for biometric data collection. MHAC measures will include blood pressure, resting heart rate, hemoglobin A1c (HbA1c), lipids, dermal carotenoids, weight and height. Seven-day accelerometer data collection will occur at baseline, mid-point, and 6-month follow-up to measure 24-h movement behavior (physical activity, sedentary time, and sleep). Geospatial data regarding access to food and physical activity resources, and resource utilization, will be collected as part of each survey timepoint. Locations of food and physical activity resources located within a 5-mile radius of the agrihood and comparison neighborhoods will be obtained via Google Distances API and mapped using ArcGIS. This will help us understand the food and physical activity resource context that these communities are located in. However, just because a resource is located proximally to a neighborhood, does not mean it is utilized (28). Therefore, we also will be asking questions to participants regarding their food acquisition and physical activity behaviors to understand how participants engage in the food and physical activity built environment. These questions include addresses of resources used, frequency of use, and time spent at resources. Survey measures for both agrihood and comparison participants include the Mediterranean Eating Pattern for Americans Screener (MEPA-16) dietary assessment (29), American Heart Association (AHA) Life’s Essential 8 (30), Perceived Stress Scale (31), and Brief Sense of Community Scale (32). The total time commitment for participants at each time point will last approximately 90 min, not including accelerometer wear time. In addition, a subsample of agrihood residents (*n* = 20) will be asked to provide an online 24-h dietary recall. See Table 1 for a detailed description of each outcome measure.

**Table 1 tab1:** Aim 1 outcome measures and their descriptions.

Measure	Description
Blood pressure	Measured in units of millimeters of mercury (mmHg) with an automated Omron sphygmomanometer. Blood pressure measurements will be repeated twice to ensure accuracy. If more than 10 mmHg difference between two measurements occurs, an additional measurement will occur. All measurements will be recorded in the study data collection form, and an average of those measures will be used in data analysis.
Heart rate	Measured in units of beats per minute (BPM) with an automated Omron sphygmomanometer concurrently with blood pressure. Heart rate measurements will be repeated twice to ensure accuracy. If more than two BPM difference between two measurements occurs, an additional measurement will be taken. All measurements will be recorded in the study data collection form, and an average of those measures will be used in the data analysis.
Hemoglobin A1c	A drop of blood will be collected using a finger prick. The drop of blood will be absorbed into a test strip that will be inserted into a small portable machine (A1CNow) that will measure the glucose in the blood. Hemoglobin A1c is measured in milligrams (mg) per deciliter (dL) of blood and the measure will be recorded in the study data collection form.
Lipids	A drop of blood will be collected using a finger prick. The drop of blood will be absorbed into a test strip that will be inserted into a small portable machine (CardioChek Plus) that will measure the lipids in their blood. Triglycerides will be measured in milligrams (mg) of triglycerides per deciliter (dL) of blood. Low-density and high-density lipoprotein (LDL/HDL) cholesterol will be measured in milligrams of LDL/HDL cholesterol per deciliter (dL) of blood. Total Cholesterol is measured in milligrams (mg) of cholesterol per deciliter (dL) of blood. All lipids will be measured using CardioChek Plus point-of-care analyzer and then recorded in the study data collection form.
Dermal carotenoids	Measured using the Veggie Meter®, which will scan the participants’ finger using light technology to measure the carotenoids and produce a score ranging from 0 to 800 (47). The higher the score, the more carotenoids are in a person’s body, indicating greater regular consumption of fruits and vegetables. An average of three consecutive measurements will be taken using the “Average of 3 Scans” mode (48). All measurements will be recorded in the study data collection form, and an average of the measures will be used in data analysis.
Weight	Recorded in kilograms. Weight measurements will be repeated to ensure accuracy. If more than a 0.1 kg difference between the two measurements occurs, a third measurement will be taken. All measurements will be recorded in the study data collection form, and an average of the measures will be used in data analysis.
Height	Measured in centimeters. Height measurement will be repeated to ensure accuracy. If more than 0.25 cm difference between two measurements occurs, an additional measurement will be taken until two consecutive measurements within 0.25 cm occur. All measurements will be recorded in the study data collection form and an average of those measures will be used in data analysis.
Online survey	The online survey will be hosted on Qualtrics (Provo, UT, USA, https://www.qualtrics.com) and is expected to take 30 min to complete. The survey assesses sociodemographics, the community food environment, fruit and vegetable consumption, stress, mood, gardening, general health, sense of community, time spent in green spaces, and physical activity. The survey will contain items from the following measures: Community Food Environment - Store Access and Shopping Behaviors (NEMS) (49), National Cancer Institute (NCI) Fruit and Vegetable Screener (50), Perceived Stress Scale (31), Gardening and Local Food – modified survey (51), Life’s Essential 8 Score (30), MEPA-16 (29), Social Connectedness and Sense of Community (52), adapted Nature Surveys (53, 54), International Physical Activity Questionnaire – Short (55), Positive and Negative Affect Scale (56), Neighborhood Social Cohesion Scale (57), Transportation Use Questions, Food and Physical Activity Resource Utilization Questions (28), UCLA Social Isolation and Loneliness Scale (58), QualityMetric’s Mean Opinion Score (MOS) Short Form (59), and sociodemographic items.
Accelerometer	We will utilize ActiGraph accelerometers (Ametris), model wGT3X-BT (https://ametris.com/actigraph-wgt3x-bt) with a wrist strap. Participants will be asked to wear the device around their wrist on their non-dominant wrist slightly above the wrist bone, like a watch. Participants will be asked to wear the device for close to 24 h each day for 7 consecutive days, including during sleep. If participants need to remove it for any reason, they will be asked to record the exact times in their log that they took the accelerometer off and put it back on. Participants will also be asked to note the time they went to sleep and the time they woke up on a paper accelerometer log.
Dietary recall (subsample)	For a subset of agrihood participants, we will utilize the National Cancer Institute (NCI) Automated Self-Administered 24-Hour Dietary Assessment Tool (ASA24) for dietary data collected via the dietary recall (https://asa24.nci.nih.gov/) (60). Through this online tool, we will ask participants to report all the foods and drinks they consumed in the last 24 h. Once they begin the dietary recall, they will have until midnight to finish entering all of the foods and drinks they consumed in the last 24 h.

To conduct Aim 2, we will recruit a subsample of adult residents living in the agrihood (*n* = 48) from the longitudinal cohort to attend a focus group and complete a time-use study. We will conduct a total of four focus groups with 12 people per group, led by trained research staff and lasting approximately 1 hour each. Topics will cover perceived positive and negative changes from living in the agrihood, consumer preferences for agrihood features and programming, including types of produce grown, ability to work on the farm, and aspects of the agrihood’s market (the Filling Station). Focus group participants will then be asked to complete a one-week time-use study. This will include once daily self-reporting via Qualtrics on neighborhood activities such as working on the farm, using the walking trails, attending events hosted at the agrihood, spending time in their home, and participating in external activities like driving, work or school, errands, and leisure activities. Focus groups participants will receive a $100 incentive for their time.

Finally, Aim 3 will be conducted as part of the agrihood resident focus groups, during which participants will be asked their reasons for moving to the agrihood, if they actively participate in the agrihood’s agricultural offerings, sales, and programs, their level of farm volunteering, and neighborhood satisfaction and place attachment. Economic benefits associated with the agrihood benefits explored in Aims 1 and 2 will be monetized. Concurrently, additional data will be acquired from the developer using a survey with items regarding break-even time, farmer compensation, maintenance costs, and public incentive programs such as open space tax credits, easements, and grants. The survey will be developed, conducted, and analyzed by a trained agricultural economist with expertise in financial analysis on the study team. Taken together, these resident- and community-level insights will provide the best current evidence base for how agrihoods create, capture, or redistribute economic value—through property-price premiums, avoided amenity costs, conservation tax policy, and diversified farm revenue.

### Participants

#### Recruitment

All recruitment activities will be overseen by trained research staff. Participants who express interest will complete a Qualtrics online screener to ascertain that they meet the inclusion criteria (described below). Interested individuals will complete the screener either independently or guided by a research staff member via phone or in person at a recruitment event. Once deemed eligible, participants will provide informed consent prior to engaging in study activities.

##### Agrihood participants

Agrihood participants, including the longitudinal cohort and focus groups, will be recruited using existing Homeowner’s Association marketing efforts, including flyers sent when homes are purchased, community fairs, front door hang tags, as well as word-of-mouth, informational presentations, phone calls, emails, website promotion, and flyers placed in community locations nearby Indigo.

##### Comparison participants

Comparison participants will be recruited using existing neighborhood marketing efforts, community fairs, front door hang tags, word-of-mouth, phone calls, website promotion, and flyers placed in community locations near the neighborhood.

#### Inclusion criteria

All participants will be adults, some of whom may be from the same household, and pregnant women may also be included. Specific inclusion criteria are below.

##### Agrihood participants

Inclusion criteria for agrihood participants are: (1) being 18 years or older; and (2) living in the agrihood as their primary or permanent residence for less than 3 months (cohort) or at least 4 months (focus group) at the time of recruitment.

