## Materials and methods

### Design and setting

The *Neighborhood & Health Study* employs a quasi-experimental prospective case–control mixed-methods approach. This entails assessing new residents of the agrihood and a comparison group over a period of 6 months (subject to a + 3-month adjustment based on actual move-in date).

The study is primarily situated at Indigo, a new 235-acre, planned 750-home agrihood located in Richmond, Texas (Fort Bend County), about 28 miles southwest of downtown Houston (18). Its developer, Meristem Communities Development Firm, is a Houston-based real estate development firm committed to creating Places for People™ which they envision as being inclusive public spaces (19). Meristem emphasizes resiliency and human-centric design by mindfully and sustainably creating places that connect land, natural systems, and people. For this reason, among others (e.g., proximity to the research team, a development timeline that aligns with the research project timeline, and Meristem’s willingness to partner), Indigo was selected for this study.

The agrihood comprises 42 acres of farm and pasture, over half of the community dedicated to open space, a 12-acre mixed-use town center with a walkable main street design and mixed retail/businesses, a 25-acre lake, integrated trails, “the Filling Station” (welcome center, café, gathering place, farm stand), vehicle-free community areas focused on nature, and spaces for residents to interact and play between rows of houses where there would traditionally be a street. Agriculture in the agrihood will be managed by Agmenity (20), a leader in the local and national agrihood movement, and will include crop fields, orchards, pasture for livestock, year-round production of seasonal produce, farm stand, farm club, agricultural education opportunities, programming, volunteer opportunities, and pastured poultry and egg production. The agrihood was designed to provide a foundational connection to agriculture and a people-first approach that fosters community connection and overall health, while being committed to environmental stewardship.

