Set to be completed in December 2026, the agrihood will include a diverse portfolio of home prices ranging from the upper $200,000’s to over $500,000 (800–3,100 sq. ft.). Median home values were $435,099 for the agrihood’s zip code in April 2025 (21, 22), demonstrating the agrihood’s commitment to providing affordable options to a diverse range of buyers in this area. Sales for homes began in March 2024 and initial move-in dates are scheduled for fall 2025. Richmond is a diverse, growing city with a racial and ethnic composition of 45.9% Non-Hispanic White, 48.5% Hispanic/Latino, 26.6% Black, and 13.8% Asian (23, 24).

The comparison community is located in Katy, Texas (Harris County), about 23-miles from the agrihood and 36-miles northwest of downtown Houston (25). The comparison neighborhood is a master-planned, non-agriculturally focused development with an estimated 2,824 single-family homes built since 2016 with build-out completion plans set for 2029. It was selected by the research team for its comparable home prices (resale values range between $419,000–$700,000 and new homes start in the $300,000’s) (21, 22) and square footage (83% 1,400–3,000 sq. ft., n = 2,011), zoning (26), and mixture of housing styles and proximity to mixed-use retail, as the agrihood. The comparison neighborhood differs from the agrihood in that its mixed-use retail is more car-dependent and not located within the community, and it is not agriculturally-integrated. However, the comparison neighborhood does have a small community garden containing 13 rentable plots, parks, connecting sidewalks, two amenity centers with physical activity options (e.g., pool, fitness center), ponds, and a prairie-land walking path. Demographically, Katy has a racial and ethnic composition of 57.4% Non-Hispanic White, 30.1% Hispanic/Latino, 12.2% Black, and 7.0% Asian (23, 24).

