##### Sample size estimation

Power was computed for a natural experiment evaluation (NEE) using Difference-in-Difference (DiD) analysis. For Aim 1, we calculated sample size for a Type I error rate alpha of 0.05, power of 0.8 for comparing the means between two groups considering physical activity outcomes of moderate-to-vigorous physical activity (MVPA); light, moderate, and vigorous physical activity (LMVPA); and time spent in sedentary behavior. Prior research has shown observed effects of moving to an activity-friendly community ranging between 10.4–10.9 min/day of MVPA, indicating small effect sizes of 0.40–0.42 (Cohen’s D) (7). We conservatively powered this study to detect a smaller effect size (Cohen’s D = 0.35). We estimate a sample size of 129 per group will provide adequate power to detect an effect size of Cohen’s D = 0.35 for all physical activity outcomes. The effect size of 0.35 is a conservative estimate based on current literature, equating to minimal detectable differences between 7.9 and 9.6 min/day for MVPA using estimates of standard deviation from previous studies (7, 33–37). This sample size is also adequate for a minimal detectable difference of 13.3 min/day for LMVPA. This sample size is adequate to detect effect sizes that are small to medium for all outcomes based on calculations for other aims. Prior community sampling of an NEE examining accelerometer-measured MVPA found a 20.64% attrition rate from baseline to year 1 and a 6.63% attrition rate from year 1 to year 2 (33). Given recently reported challenges to NEE recruitment, we conservatively overestimate attrition rates, necessitating a sample size of 175 for the agrihood and comparison groups.

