### Data collection

The research team conducted an initial survey of demographic and health indicators, neighborhood design preferences, and willingness to pay for specific amenities among 128 prospective buyers of the agrihood between March and July 2024 (Baylor IRB #2158321–1). Findings from the survey provided a formative understanding, which helped to inform the design of the present study and served as a project pilot test for survey recruitment and enrollment procedures (39, 40).

Beginning in Spring 2025, data collection began across three time points (pre-move-in, 3 months after move-in date, and 6 months after move-in date) by trained research and clinical staff (see Table 1). Over the course of 6 months, agrihood participants will be asked to complete (1) three 30-min online surveys; (2) two 30-min in-person health assessments collecting height, weight, blood pressure reading, heart rate, dermal carotenoid scan (Veggie Meter®), HbA1c (finger prick), and lipids (finger prick); (3) three 7-day consecutive accelerometer wears; and (4) three 30-min online dietary recalls (subsample). Comparison participants will be asked to complete three 30-min online surveys at 0 months, 3 months, and 6 months from recruitment.

The focus groups are planned to occur starting in the Fall of 2025. The accompanying one-week time-use study, entailing once-daily self-reports, will begin the following day after each of the four focus group sessions. The gathering of economic data will occur during focus group discussions and concurrently with the agrihood developer as homes continue to be built and residents move into the new units. The developer survey will be designed to capture the full economic arc of an agrihood project—from conception to financial stabilization—by prompting developers to narrate each phase of development (e.g., project origins and strategic intent, land acquisition and zoning, entitlement and permitting processes, capital investment structures, farm-related costs and revenue projections, marketing, sales absorption rates, and plans for long-term stewardship).

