### Data analysis

For Aim 1, we will compare the changes in physical activity outcomes (moderate to vigorous physical activity [MVPA], light, moderate, and vigorous physical activity [LMVPA], walking, sedentary behavior) between the agrihood and comparison participant groups across three time points (Agrihood: pre-move-in, 3 months after move-in date, 6 months after move-in date; Comparison: 0, 3, 6 months) using DiD analysis (linear mixed-effects longitudinal models). Regression models will include the group, time period, and the group by time period interaction terms. Random cluster effects will be included to account for correlations between participants in the same neighborhood and *a priori* covariates of age, sex, and educational attainment. Random effects for the participants will be included to account for correlation in observations. To address multicollinearity, we will assess variance inflation factors (VIF > 5) and pairwise correlations (|r| > 0.70); collinear variables will be excluded, combined, or tested in sensitivity analyses to avoid attenuation of the group × time effect. Confounders showing baseline imbalance (standardized mean difference > 0.10) will be prioritized for inclusion. Restricted maximum likelihood will be used for complete case analysis to incorporate all available data, and intention-to-treat analysis will include all participants included at baseline. Multiple imputation will be used to estimate missing data points and standard errors. Imputations will follow standardized procedures, including auxiliary variables, and will follow hierarchical approaches. We will examine the potential for missingness of data to not be at random by comparing baseline characteristics of participants who have completed physical activity data with those who do not. If there are differences by age, education, race, or self-reported perceived health, any variables that differ will be used as an auxiliary variable in multiple imputation. Fraction of missing information will be used to measure level of uncertainty about the values imputed for missing values. We will use a number of imputations that satisfy the recommendation to have the number of imputations (at least) equal the highest fraction of missing information (FMI) percentage. Using the geographic information system (GIS) data and resulting maps, for physical activity resources we will: (1) count the number of resources located within the 5-mile network buffer using ArcGIS; (2) measure the distances to the closest resources for different types of resources (e.g., closest park or trail) using ArcGIS and Google Distances API; (3) assess how these counts and distances change over time; and (4) assess changes in time spent in transportation to go to resources. Specifically, we will compare the changes in number of physical activity resources, distance (in miles) to closest objectively measured resources, and distance (in miles) to utilized resources and associated transportation-related time spent between the groups across 3 time points (Agrihood: 0, 3 months after move-in date, 6 months after move-in date; Comparison: 0, 3, 6 months) using DiD analysis, and assess if any of these variables are associated with device-measured physical activity outcomes using linear mixed-effects multilevel models. All statistical analysis will be conducted using SAS and/or R software. We will also generate maps showing changing patterns in physical activity resource utilization in ArcMap. This two-pronged approach of mapping and analyzing objective physical activity environments as well as physical activity resource utilization and time use behaviors are important to better understand how the built environment in these communities are or are not conducive to physical activity, as well as how participants are (or are not) engaging in the resources designed to promote physical activity.

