Our study design has several strengths, including multiple matched cohorts of residents. In addition, we propose a strong data-driven approach involving biological data collection from the mobile health assessment clinics and device-captured physical activity, along with highly valid and reliable self-report measures that capture individual and community-level preferences and perspectives. Given our multi-disciplinary team and established partnerships with the developers, we anticipate the aims will be achievable, and the results generated from this work will translate into meaningful considerations for residents of these neighborhoods. Moreover, we believe the results will allow us to understand not only how agrihoods affect health and wellbeing, but also how residents engage with them, thereby informing future models for development that are effective for improving health and are economically sustainable.

Given funding and scope of work parameters, this study also has several limitations worth noting. First, the comparison community consists of existing residents, meaning we are unable to capture their baseline prior to moving in, unlike with the agrihood participant sample. Capturing residents as they move into a new development is extremely challenging, and it was not feasible to find a comparison community that was being occupied at the same time as the agrihood. Second, due to budgetary constraints, accelerometer-based physical activity measurement and biological data collection are only feasible among participants in the agrihood community, which may reduce cross-group comparability. Third, the funding support received for this work only covers 13 months, thereby allowing for 6 months of follow-up which may be too short to observe meaningful or sustained behavioral and health changes.

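### The agrihood cohort criterion requires people to live there already, but the difference-in-differences analysis takes their baseline as measured before move-in; both cannot hold

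*Protocol article*

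**What the plan says.** **Eligibility.** The inclusion criteria for agrihood participants require a cohort member, when recruited, to be "living in the agrihood as their primary or permanent residence for less than 3 months (cohort"). The Recruitment section puts the eligibility screener first, then consent, then study activities.

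**Baseline timing.** The Data collection section says that "data collection began across three time points (pre-move-in, 3 months after move-in date, and 6 months after move-in date"). The Data analysis section uses the same scheme for the physical activity DiD: "Agrihood: pre-move-in, 3 months after move-in date, 6 months after move-in date; Comparison: 0, 3, 6 months". For resource and dietary outcomes, the same section labels the first agrihood time point 0 instead.

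**Claim about the baseline.** In the limitations, the authors say of the comparison residents that "we are unable to capture their baseline prior to moving in, unlike with the agrihood participant sample".

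**Calendar.** "Beginning in Spring 2025, data collection began", whereas under Design and setting "initial move-in dates are scheduled for fall 2025". That section also makes the 6-month period "subject to a + 3-month adjustment based on actual move-in date", without further explanation.

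**The concern.** The stated purpose is to assess the effect of relocating to the agrihood. The comparison residents do not move, so the agrihood baseline is the only measurement meant to fall before the exposure. If it is taken after move-in, any early change in activity, diet or connectedness is counted as part of the starting level and drops out of the estimated effect.

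The criterion allows a gap of anything up to 3 months. If follow-up stays tied to the move-in date, a person recruited late in that window has the baseline and the 3-month visit close together, and the first interval carries little information.

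Accelerometry and the physical assessments are done only in the agrihood group. For them, change from baseline is the whole contrast, and no comparator is available to offset a badly timed baseline.

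The two rules also define different populations. One excludes everybody who has not yet moved; the other needs exactly those people.

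**Working it through.** **Step 1: can the statements be reconciled?**

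- Criterion: resident at recruitment, for less than 3 months.
- Sequence: screening, consent, then study activities, so baseline follows recruitment.
- Therefore baseline follows move-in for every person who meets the criterion as written.
- Data collection, Data analysis and Discussion: baseline precedes move-in.

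These conflict. The calendar shows the same thing: with collection starting in spring 2025 and first move-ins set for fall 2025, nobody could have met the residence criterion when collection began. The move-in adjustment does not say how a baseline taken after move-in is to be treated.

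**Step 2: reproduce the plan's own figures.** Inputs from Sample size estimation: "Type I error rate alpha of 0.05, power of 0.8 for comparing the means between two groups", d = 0.35, attrition of 20.64% then 6.63%. Sidedness is not stated; two-sided is assumed because it reproduces the plan.

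- Normal approximation: n = 2 × (1.960 + 0.842)² / 0.35² = 2 × 7.85 / 0.1225 ≈ 128. The t-based solution is 129.1, which agrees with the stated 129. A one-sided test would give 101.
- Power at 129 per group: 80.3%.
- Compounded attrition: 1 − (1 − 0.2064)(1 − 0.0663) = 0.259. Then 129 / 0.741 ≈ 174.1, rounded up to 175, as stated.

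The sample-size arithmetic is therefore sound. What is in question is what the contrast measures.

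**Step 3: effect of a post-move baseline.** Let f be the share of agrihood participants whose baseline falls after move-in, and g the average share of the effect already present at that baseline. Assume the comparison group's change is otherwise a valid counterfactual and the standard deviation is unchanged. Then

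expected d = 0.35 × (1 − f × g).

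The article gives neither f nor g, so the table shows a range of assumptions.

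| f | g | expected d | power at 129 per group | n per group for 80% |
|---|---|---|---|---|
| 0 | any | 0.350 | 80% | 129 |
| 0.5 | 0.25 | 0.306 | 69% | 168 |
| 0.5 | 0.5 | 0.2625 | 56% | 228 |
| 1 | 0.5 | 0.175 | 29% | 513 |

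To put g on a time scale: if the effect built up linearly over 6 months, a baseline k months after move-in would give g = k/6. That is 0.25 at 1.5 months and 0.5 at 3 months. Linear build-up is an assumption without support in the article. The last row puts every participant at 3 months, which the criterion itself excludes, so on that scale it is a bound.

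**Step 4: direction.** The formula also accepts a negative g. If settling in temporarily lowers activity, baseline sits below the true starting level, 1 − f × g exceeds 1, and the contrast is inflated.

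**The case against.** Much of the article points to enrolment before the move, with a badly worded criterion. Flyers go out when homes are purchased, the Discussion ties enrolment to households under contract, and collection starts before the first move-ins. The 3-month limit may be meant only as a ceiling on residence. The move-in adjustment has the same length as that window, so the authors evidently foresaw variation in timing and may intend to shift the later visits. On this reading, a baseline that is systematically late is not shown. **This stands** as a limit on what can be claimed. It does not remove the conflict: the criterion requires residence, and no rule covers those who enrol after moving.

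A reader might infer that the DiD is biased toward no effect, or that the study has only 29% to 56% power. The article does not support either as a finding. Bias toward no effect needs an effect that begins soon after the move and then persists or grows. The power figures depend on f and g, which are unknown. They also use the physical activity calculation. The comparison group wears no accelerometer, so the figures do not describe an available device-based comparison and do not carry over to diet or connectedness.

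It can also be objected that making pre-move participants the main analysis set would depart from the planned intention-to-treat set of everyone included at baseline. That is right, and the fix below keeps that set.

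**Conclusion.** The contradiction is certain and rests on the article's own text: a person who meets the cohort criterion as written cannot have the pre-move baseline that the analysis uses and the Discussion claims. Any participant enrolled under that wording contributes a post-exposure value to the pre-exposure period of the DiD.

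Dilution is the more likely consequence, but its direction is not assured and its size cannot be derived from the article. The illustrative range runs from the planned 80% power, if all baselines truly precede the move, through 69% and 56%, to 29% as a bound. It assumes a two-sided test, 129 evaluable per group, d = 0.35 and the chosen values of f and g. How many baselines actually fell after move-in is not stated, and it may be few.

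**What to change.** Reword the cohort criterion to admit adults under contract or with a scheduled move-in who complete the baseline before moving. If enrolment up to 3 months after move-in is kept:

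- record days from move-in to baseline for every agrihood participant;
- do not code a post-move baseline as pre-move-in, but model actual time since move-in;
- keep all participants in the intention-to-treat set;
- prespecify an additional analysis restricted to true pre-move baselines;
- state what the move-in adjustment does to the visit schedule, and use one label for the agrihood baseline across outcomes;
- correct the Discussion's statement that the agrihood baseline precedes the move.

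**Cost.** This means an amendment to one criterion, one extra date variable, and a time variable in the model in place of visit labels. Collection has begun and recruitment is limited by the number of households under contract, so some post-move enrolment may be unavoidable. The restricted analysis is then smaller and less precise. For example, if half of 129 agrihood participants qualified against 129 comparison participants, the standard error would be √[(1/64.5 + 1/129) / (2/129)] = √1.5 ≈ 1.22 times the planned one. For that reason it is proposed as an addition to the intention-to-treat analysis and not as a replacement.
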